## Abstract

**Background:**

Gonorrhoea is one of the most common sexually transmissible infections in men who have sex with men (MSM). Gonorrhoea rates have increased substantially in recent years. There is concern that increasing gonorrhoea prevalence will increase the likelihood of worsening antibiotic resistance in *Neisseria gonorrhoeae*. A recent randomised controlled trial (RCT) demonstrated that a single-dose of mouthwash has an inhibitory effect against oropharyngeal gonorrhoea. We are conducting the first RCT to evaluate whether daily use of mouthwash could reduce the risk of acquiring oropharyngeal gonorrhoea.

**Methods/design:**

The OMEGA (Oral Mouthwash use to Eradicate GonorrhoeA) study is a double-blind RCT and will be conducted at several sexual health clinics and high caseload General Practice (GP) clinics in Melbourne and Sydney, Australia. A total of 504 MSM attending the participating sites will be recruited. Participants will be randomised to either using ‘Study mouthwash A’ or ‘Study mouthwash B’ for 12 weeks. Study mouthwash A was inhibitory against *N. gonorrhoeae* in vitro, whereas study mouthwash B was not. Participants will be instructed to rinse and gargle the study mouthwash for 60 seconds every day. The primary outcome is the proportion of participants with oropharyngeal gonorrhoea detected by nucleic acid amplification test by 12 weeks.

**Discussion:**

The results from this trial may provide a novel way to reduce gonorrhoea prevalence and transmission without the use of antibiotics that may be associated with development of resistance. If shown to be effective, the widespread use of mouthwash will reduce the prevalence of oropharyngeal gonorrhoea, which plays key role in driving the emergence of gonococcal antimicrobial resistance through DNA exchange with oral commensal bacteria. The anticipated net effect will be interruption of onward transmission of *N. gonorrhoeae* within high density sexual networks within MSM populations.

**Trial registration:**

Australian New Zealand Clinical Trials Registry ACTRN12616000247471, registered on 23rd February 2016.

## Background

*Neisseria gonorrhoeae* is the causative agent of one of the most common sexually transmissible infections (STIs) worldwide and in recent years has increased substantially in Australia [1] and in other high income countries [2–4]. It is estimated that there were 78 million new cases of gonorrhoea among individuals aged 15–45 years globally in 2012, with over 55% in males [5].

Australian national surveillance data show that the gonorrhoea notification rate in men was stable between 2006 and 2009 (around 50 cases per 100,000 male population). However, rates have increased substantially since 2010 reaching 117 cases per 100,000 male population in 2015 [1] with the majority of cases occurring in men who have sex with men (MSM). Rises in other STIs such as syphilis and increasing rates of previously uncommon diseases such as lymphogranuloma venereum (LGV) are further evidence of the overall rising STI trend among MSM [6–10]. In addition, STIs can also increase the risk of HIV acquisition [11–13]. Biomedical interventions for HIV such as pre-exposure prophylaxis (PrEP) and ‘Treatment as Prevention’ (TasP) have been shown to reduce the risk of HIV transmission [14–18]. However, these interventions have been associated with an increase in the number of sexual partners and a decrease in condom use for anal sex, practices associated with increased risk of STIs [15, 19–21]. With the scale up of PrEP in Australia and elsewhere [22, 23], STIs including gonorrhoea are likely to rise further [24].

The rising number of gonorrhoea cases is of particular concern because gonorrhoea is becoming more difficult to treat [25]. Gonorrhoea has become resistant to almost all previously recommended treatments and successful treatment currently relies on use of the last main class of antimicrobial agents suitable for first-line therapy, specifically extended spectrum cephalosporins such as ceftriaxone [26]. To reduce the emergence of further resistance, ceftriaxone is now frequently given with a second antibiotic, typically single-dose azithromycin, as dual therapy [27–29]. Extensively antibiotic-resistant *N. gonorrhoeae* isolates have been reported in a few countries in recent years but these strains not yet spread widely [30–36]. As there are very limited options for treating these strains of *N. gonorrhoeae* [37–40], *N. gonorrhoeae* is considered as an ‘urgent resistance threat’ by the US Centers for Disease Control and Prevention (CDC) [41], a ‘priority organism’ in the Australian National Antimicrobial Resistance Strategy [42] and a ‘global threat’ by the World Health Organization (WHO) [43, 44]. One key strategic objective of the WHO Global Action Plan [45] to prevent the emergence of multidrug and cephalosporin-resistant gonorrhoea is to reduce the prevalence of infection, particularly in the oropharynx where resistance is thought to be developed via spontaneous mutation as well as genetic exchange of resistance genes with commensal *Neisseria spp.* cohabiting the same environment [46, 47].

To reduce the prevalence of gonorrhoea, it is important to understand the transmission dynamics and main drivers of gonorrhoea incidence in MSM. One might assume that gonorrhoea incidence is largely driven by penile-anal sex [48], in a similar manner to chlamydia [49]. However, unlike chlamydia, where infection is mostly asymptomatic [50, 51], urethral gonorrhoea is usually symptomatic within weeks and therefore rapidly treated in well-resourced settings like Australia [52, 53]. Urethral gonorrhoea has little opportunity to facilitate transmission to other anatomical sites because it is infectious for such a short time [54]. The second major difference is that gonorrhoea very commonly infects the oropharynx, while chlamydia does so infrequently [55–58]. In Australia, oropharyngeal gonorrhoea positivity among MSM attending a sexual health service was around 8% [56] and oropharyngeal chlamydia positivity was around 1% [59, 60]. A case-control study in Seattle-King County estimated that the population attributable risk fraction of urethral gonorrhoea due to insertive penile-oral sex is about 33%, while the population attributable risk fraction of urethral chlamydia due to insertive penile-oral sex is only 3% [61]. A considerable proportion of the sexual practices that are potentially responsible for gonorrhoea transmission involve exposure to the oropharynx, these sexual practices include kissing, oral sex, rimming (oral-anal sex) and the use of saliva as a lubricant during anal sex [48, 62, 63]. Gonorrhoea is also commonly found in expectorated saliva [64]. This was first identified 30 years ago where *N. gonorrhoeae* was cultured from the saliva of 67% of individuals with culture positive oropharyngeal swabs [65]. We recently repeated this work and found that almost half of those (43%) who were culture positive in the oropharynx also were also culture positive in the saliva sample, and all (100%) had a positive result in their saliva by a nucleic acid amplification test (NAAT) [66]. Saliva is commonly used in various sexual activities among MSM and it is our hypothesis that saliva plays a key role in gonorrhoea transmission among MSM [48]. Indeed, kissing has been reported to be the most common sexual behaviour among MSM [67], and gonorrhoea could possibly be transmitted by kissing [48, 62, 68, 69]. Saliva use as a lubricant during anal sex is common among MSM (~70%) [63, 70], and a similar proportion (~70%) of MSM practise rimming [63]. The relatively short duration to spontaneous resolution of untreated oropharyngeal gonorrhoea (<12 weeks) compared to anorectal gonorrhoea (~12 months) [71], means high rates of partner change are required to sustain such a high prevalence of oropharyngeal gonorrhoea [72]. This may be the key reason it is mainly seen in MSM who have large numbers of sexual partners [52].

We hypothesise that it is important to reduce the prevalence and incidence of oropharyngeal gonorrhoea to reduce the overall burden of gonorrhoea [48]. This is because both the prevalence and incidence of gonorrhoea is largely driven by infections at anatomical sites where infections are predominantly asymptomatic, and therefore undetected and untreated, allowing ongoing transmission. In MSM, gonococcal infections at extra-genital sites (i.e. oropharynx and anorectum) are mainly asymptomatic [73–76]. This is also supported by recent mathematical modelling suggesting approximately 75% of incident cases of oropharyngeal gonorrhoea were transmitted from oropharynx to oropharynx through kissing [77], adding weight to another model which suggests gonorrhoea may not be eliminated from the MSM population even with 100% condom-use for anal sex [78]. The implications of these findings for the control of gonorrhoea are clear. If major reductions in gonorrhoea are to be achieved in MSM population, it is essential to reduce gonorrhoea transmission from the oropharynx.

Options for reducing oropharyngeal gonorrhoea cases include use of condoms for oral sex, very frequent screening, antibiotic prophylaxis or use of other agents that could act to prevent the acquisition of infection such as our proposed mouthwash intervention. Given that condom use for anal sex is decreasing [79–81] and MSM rarely use them for oral sex [82], the 3-month average duration of gonorrhoea means that screening would need to be at least every 3 months, as recommended for high-risk Australian MSM [83] but this has been shown to be difficult for MSM to sustain [84]. Antibiotic prophylaxis is unlikely to be adopted because of concerns about emerging resistance. There is no vaccine against gonorrhoea [85]. Thus, mouthwash represents a novel and attractive alternative intervention.

In a recent in vitro study, we showed that 60 seconds of exposure to a commercial alcohol-containing mouthwash product at dilutions of up to 1 in 4, has an inhibitory effect on *N. gonorrhoeae* when assessed at 48 h [86]. In addition, in a small RCT, of 58 MSM who were culture positive for oropharyngeal gonorrhoea, men who were allocated to rinse and gargle the intervention solution (i.e. alcohol-containing mouthwash) for 60 seconds had a significantly lower proportion of positive cultures from the oropharyngeal surface 5 min after use of mouthwash compared to those who were allocated to rinse and gargle the control solution (saline) (52% versus 84%; *p* = 0.013) [86].

### Research hypothesis and aim

The aim of this study is to determine if daily use of antibacterial mouthwash will reduce the incidence of oropharyngeal gonorrhoea in MSM over 12 weeks. We hypothesise that daily use of antibacterial mouthwash could potentially reduce the risk of acquiring oropharyngeal gonorrhoea when used every day and hence reduce the overall incidence of oropharyngeal gonorrhoea.

## Methods/Design

### Trial registration

The trial has been registered on the Australian and New Zealand Clinical Trials Registry (ACTRN12616000247471) on 23rd February 2016.

### Trial design

The OMEGA (Oral Mouthwash use to Eradicate GonorrhoeA) study is a double-blind randomised controlled trial (RCT) of daily use of an antibacterial mouthwash to reduce the risk of acquiring oropharyngeal gonorrhoea in MSM. The trial will be of 12 weeks duration for each participant.

This trial will be conducted within sexual health clinics and high STI-caseload General Practice (GP) clinics in Melbourne and Sydney, Australia. This trial will be conducted in accordance with the guidelines for Good Clinical Practice and reported in accordance with the CONSORT guidelines [87].

### Eligibility criteria for participants

This study is limited to men who have sex with men.

#### Inclusion criteria

Men who have sex with men and aged 16 years or above, and fulfil either (i) or (ii).(i)Men aged 16–24 years: tested positive or negative for oropharyngeal gonorrhoea by NAAT within the previous 30 days, as young MSM are at higher risk of oropharyngeal gonorrhoea [80].(ii)Men aged 25 years or above: tested positive for oropharyngeal gonorrhoea by NAAT within the previous 30 days, as this population has a higher rate of repeat diagnosis of gonorrhoea within 90 days [88].
Provide written informed consent.Provide consent for the research team to contact their health professional and/or GP to clarify the use and name of any antibiotics used during the study period.Have sufficient English language proficiency to understand the study requirements.Men co-infected with HIV or other STIs are eligible.

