#### Secondary outcomes

There are several secondary outcomes in this trial.Proportion of MSM diagnosed with oropharyngeal gonorrhoea by culture within 12 weeks.Adherence to mouthwash over 12 weeks.Acceptability and tolerability of using mouthwash.The proportion of MSM with any of: gonorrhoea at other anatomical sites (urethra and anorectum) or newly acquired chlamydia, HIV or syphilis infection by week 12.

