#### Baseline

Participants will be asked to complete a questionnaire at the baseline visit will be conducted at the participating clinics.

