#### Saliva

Participants will be required to self-collect a saliva sample every 3 weeks. Figure 4 illustrates how to self-collect a saliva sample. This instruction sheet will be given to the participants and a video clip is available on the OMEGA study website for participants to review the procedure (www.mshc.org.au/omega). In brief, participants will be instructed to accumulate saliva in the mouth for about 30 seconds to get a reasonable volume of saliva. Participants will spit as much saliva as possible into a yellow cap specimen collection jar, and saliva will be collected by using an UriSwab (Copan Diagnostics, Brescia, Italy). Saliva samples at week 6 and week 12 will be collected at the participating clinic under the research nurse’s supervision; while saliva samples at week 3 and week 9 will be collected at home by participants. All saliva specimens collected will be transported by using UriSwab.

All participants will be required to send their home-based collected UriSwabs to the Melbourne Sexual Health Centre at week 3 and 9 by post. The research nurse at each participating clinic will be required to send clinic-based collected UriSwabs to the Melbourne Sexual Health Centre at week 6 and 12 by post.

Once the research team at the Melbourne Sexual Health Centre receives the UriSwab by post, the UriSwab will be immediately centrifuged at 1200 g for 1 min to separate the saliva from the UriSwab sponge. The centrifuged saliva will be pipetted into a sterile 2.0 mL micro tube (Scientific Specialties, Inc., CA, USA) and stored at −80 °C freezer at the Melbourne Sexual Health Centre for testing.

All centrifuged saliva samples will be batch tested at the Royal Women’s Hospital, Molecular Microbiology Laboratory, Melbourne. The saliva samples will be placed on the MagNA Pure 96 Instrument (Roche Diagnostics, Mannheim, Germany) for DNA purification and will be assessed for sampling and extraction adequacy by amplifying a 260 bp region of the human beta-globin gene [95]. The gonococcal bacterial DNA load of the sample will be quantified using qPCR assays targeting the *N. gonorrhoeae opa* gene. All samples positive for the *opa* gene will then be confirmed using a qPCR targeting the *N. gonorrhoeae porA* gene [96, 97].

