#### Oropharyngeal swabs

Pharyngeal specimens will be collected at week 6 and week 12 clinic visits. All oropharyngeal swabs will be collected by the research nurses at each participating site. All swabs will be taken by no more than two research nurses at each site to minimise the variability of sampling technique [98]. All research nurses at each site will be trained on how to take a oropharyngeal specimen for this study, and an instruction sheet and a video clip will be provided to the research nurses to review the procedure (Fig. 5).

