#### Primary analysis

The primary end-point will be the proportion of men who have gonorrhoea detected in the oropharynx by NAAT at any time within 12 weeks in any specimen (saliva and/or oropharyngeal swabs). The proportion of men with oropharyngeal gonorrhoea detected will be compared between both groups. The 95% confidence intervals (CI) of the proportion of men with oropharyngeal gonorrhoea will be calculated based on the ‘exact’ binomial confidence intervals [106]. The two study arms will be compared using logistic regression. Multivariate logistic regression will be performed to adjust any imbalance of baseline characteristics and potential confounding factors. Men with symptomatic urethral gonorrhoea may attend clinical services between the two clinic visits and test positive for oropharyngeal gonorrhoea. Any positive oropharyngeal results will be included in the analysis unless they were taken within 3 weeks of treatment because within 3 weeks NAAT results may represent residual non-viable DNA from the previous infection [107].

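### With no specimen at week 0, infections present at entry can count as primary events, and the STIs promised as newly acquired mostly cannot be told from pre-existing ones

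*Protocol article*

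**What the plan says.** The research aim and the trial design section both speak of incidence and of the risk of acquiring oropharyngeal gonorrhoea.

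- **Entry.** Men aged 16–24 qualify if they "tested positive or negative for oropharyngeal gonorrhoea by NAAT within the previous 30 days". Men aged 25 or above must have "tested positive for oropharyngeal gonorrhoea by NAAT within the previous 30 days, as this population has a higher rate of repeat diagnosis". Also, "Men co-infected with HIV or other STIs are eligible". The eligibility criteria state no condition on treatment or clearance before randomisation.
- **Week 0.** Under Baseline: "Participants will be asked to complete a questionnaire at the baseline visit". In Table 2 every biospecimen row is empty at week 0.
- **Follow-up.** "Pharyngeal specimens will be collected at week 6 and week 12 clinic visits". Saliva is taken at weeks 3, 6, 9 and 12; "saliva samples at week 3 and week 9 will be collected at home by participants". Urine, anorectal swab and serology are taken at week 12 only (Table 2; Full STI screening at week 12).
- **Primary end-point.** A positive NAAT in saliva or swab at any time in the 12 weeks. "Any positive oropharyngeal results will be included in the analysis unless they were taken within 3 weeks of treatment".
- **Secondary outcome.** Gonorrhoea at other sites, or "newly acquired chlamydia, HIV or syphilis infection by week 12". The Secondary analysis section describes the same outcome simply as men who have other STIs by 12 weeks.

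**The concern.** To measure acquisition one must know who was uninfected at the start. Here the last known status may be a month old, and for many men it is positive. The 3-week rule deals with residual DNA after treatment. It does not remove an infection gained between a negative qualifying test and week 0, an infection still untreated at entry, or a reinfection after treatment but before randomisation. The Background gives an average duration of about 3 months, so such infections could still be detectable at week 3 or 6 and would then count.

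Two things are at stake. If mouthwash prevents new infections but leaves established ones alone, events that it could not prevent enter both arms and shrink the observed contrast. And the secondary outcome would be reported as new infection when the schedule mostly yields prevalence at week 12.

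**Working it through.** **1. The planned figure.** Inputs from Sample size: 20% versus 10%, 5% significance (two-sided assumed), 80% power, 1:1.

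Uncorrected: n = [1.96·√(2·0.15·0.85) + 0.842·√(0.20·0.80 + 0.10·0.90)]² / 0.10² = 198.96.

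With continuity correction: n′ = (n/4)·[1 + √(1 + 4/(n·0.10))]² = 218.5, so 219 per arm and 438 in total. This is the stated figure. The same formula reproduces the other five cells of Table 1.

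**2. How many men might be infected at entry?** The documents do not say. As a guide, take the planned control risk as a constant hazard: h = −ln(0.8)/84 = 0.00266 per day.
- Infected within 15 days of a negative test: 1 − exp(−15h) = 3.9%.
- Infected within 30 days: 1 − exp(−30h) = 7.7%.

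These apply only to men whose qualifying test was negative, all of whom are aged 16–24. If half of all men qualified that way (an assumption), the 15-day figure is 0.5 × 3.9% ≈ 2% of all men. Index-positive men who were untreated or reinfected would add an unknown amount. A range of 1–4% of all men is used below, as an assumption.

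**3. Effect on power.** Let p0 be the share infected at entry. Assume that mouthwash does not affect these infections, that it halves new ones, and that they come on top of the planned rates. Then each arm's observed rate is 1 − (1 − risk)(1 − p0).

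Power = Φ{[|p1 − p2| − 1/n − 1.96·√(2p̄(1 − p̄)/n)] / √[(p1(1 − p1) + p2(1 − p2))/n]}, n = 219.

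| p0 | Control | Intervention | Risk ratio | Power |
|---|---|---|---|---|
| 0 | 20.0% | 10.0% | 0.50 | 80% |
| 1% | 20.8% | 10.9% | 0.52 | 77% |
| 2% | 21.6% | 11.8% | 0.55 | 75% |
| 4% | 23.2% | 13.6% | 0.59 | 70% |

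For p0 = 4%: (0.096 − 0.0046 − 0.0726)/0.0367 = 0.51, and Φ(0.51) ≈ 0.70.

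**4. Two assumptions that move the answer.**
- *Clearance.* If mouthwash cleared half of a 4% prevalence, the rates are 23.2% and 1 − 0.90 × 0.98 = 11.8%, and power is 86%. The loss disappears.
- *Composition of the 20%.* If the planned 20% already contains the entry infections, the intervention rate is p0 + 0.5 × (0.20 − p0). For p0 = 1%, 2% and 4% this gives 10.5%, 11.0% and 12.0%, with power 75%, 70% and 58%. Sample size does not break down the 20%.

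**5. Under the null.** If mouthwash has no effect, p0 is the same in expectation in both arms, and so are the observed rates. The type I error is not affected.

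**6. The secondary outcome.** This needs no arithmetic. Chlamydia and syphilis have one study test, at week 12, in men who may have entered with either infection. No baseline comparator is named. HIV differs in part: the footnote to Table 2 says that HIV-positive men are not tested for HIV, so known HIV is not counted as new; undiagnosed HIV at entry would be.

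**The case against.** The strongest reply is that the primary end-point is worded as diagnosis or detection and so measures what it says. Randomisation balances prevalent infections on average, and any dilution is conservative. This stands: there is no bias between arms under the null. What remains is the gap between that end-point and an aim framed as acquisition.

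Second, the size and even the direction of the power effect rest on assumption. A reader might apply the 30-day figure of 7.7% to everyone and infer a severe loss of power. The documents do not support that: it would need every participant to be index-negative with a test a full 30 days old, whereas men of 25 or above must be index-positive. The hazard is also borrowed, because the 20% was built from repeat positivity after a positive test. If half the men are index-negative and the hazard is lower, the share infected could be about 0.8% and power 78%.

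Third, the pilot trial in the Background found fewer positive cultures 5 minutes after mouthwash in men already infected (52% versus 84%), so some action on existing infection is possible. But short-term culture inhibition is not NAAT clearance, and the Discussion says that mouthwash is not meant as treatment. The point leaves the direction open; it does not remove the concern.

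Fourth, a reader might infer that no newly acquired STI can be identified at all. That goes too far: known HIV is excluded, and routine clinic results may exist for some men. The article does not require those results or use them as a baseline.

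**Conclusion.** The concern holds in two limited parts.

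**Primary end-point.** Infections present at randomisation can count as events in both arms of a trial that aims at acquisition. The comparison stays valid under the null. Dilution is possible but not established, because neither the mix of index-positive and index-negative men nor the gap between test and baseline is given. With 1–4% of all men infected at entry, unaffected by mouthwash and added to 20% versus 10%, power at 219 per arm is about 77% to 70%. The loss is larger if the planned 20% already includes these men, and there is none if mouthwash clears them. These figures are illustrations, not estimates.

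**Secondary outcome.** This part needs no numerical assumption. The label promises new infection, the schedule gives one test at week 12, and the Secondary analysis section describes men who have an STI by then. Apart from known HIV, new and pre-existing infection cannot be separated as planned.

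**What to change.** **(a) Secondary outcome.** Reword it to match the Secondary analysis section, as detected at week 12. Alternatively, count a case as new only where a documented clinic result at the qualifying visit was negative, or the earlier infection was documented as treated. Otherwise draw no conclusion about acquisition of these STIs. The rewording costs nothing; the alternative needs retrieval of clinic results.

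**(b) Week-0 sample.** For participants still to be enrolled, have one saliva sample self-collected at the baseline visit with the existing kit, frozen, and batch-tested with the others. Leave the primary end-point and population unchanged. Pre-specify a sensitivity analysis that excludes or adjusts for week-0 positives, reported by qualifying result and treatment date, because a positive in a recently treated man may be residual DNA. For the same reason, do not restrict the primary analysis to week-0 negatives: that would remove treated index-positive men, whom the trial recruits for their higher risk.

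Discounting a positive in the first on-study specimen is not a substitute. An infection set aside at week 3 could still count at week 6. In index-negative control men the rule would also discard more new infections (1 − exp(−21h) = 5.4% acquired by week 3) than the 3.9% expected to be present at entry after a 15-day gap.

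The cost of (b) is one tube and one assay per future participant. Recruitment began in March 2016, so men already enrolled will have no week-0 sample. The other four sites were expected to start in June 2017, so their participants could be covered if the change is made in time.
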